## Abstract

**Background:**

Protracted bacterial bronchitis (PBB) is an endobronchial infection and a the most common cause of chronic wet cough in young children. It is treated with antibiotics, which can only be targeted if the causative organism is known. As most affected children do not expectorate sputum, lower airway samples can only be obtained by bronchoalveolar lavage (BAL) samples taken during flexible bronchoscopy (FB-BAL). This is invasive and is therefore reserved for children with severe or relapsing cases. Most children with PBB are treated empirically with broad spectrum antibiotics. CLASSIC PBB will compare the pathogen yield from two less invasive strategies with that from FB-BAL to see if they are comparable.

**Methods:**

131 children with PBB from four UK centres referred FB-BAL will be recruited. When attending for FB-BAL, they will have a cough swab and an induced sputum sample obtained. The primary outcome will be the discordance of the pathogen yield from the cough swab and the induced sputum when compared with FB-BAL. Secondary outcomes will be the sensitivity of each sampling strategy, the success rate of the induced sputum in producing a usable sample and the tolerability of each of the three sampling strategies.

**Discussion:**

If either or both of the two less invasive airway sampling strategies are shown to be a useful alternative to FB-BAL, this will lead to more children with PBB having lower airway samples enabling targeted antibiotic prescribing. It would also reduce the need for FB, which is known to be burdensome for children and their families.

**Trial registration number:**

ISRCTN79883982.

WHAT IS ALREADY KNOWN ON THIS TOPICProtracted bacterial bronchitis (PBB) is an endobronchial infection and the most common cause of chronic wet cough in children from the developed world.Identifying the causative organism in PBB allows a narrower spectrum antibiotic to be used which decreases the risk of antibiotic resistance.Children with PBB rarely expectorate sputum and the only widely used strategy to sample the lower airway is flexible bronchoscopy (FB). As this is invasive, it is reserved for severe or recurrent cases meaning most children with PBB are treated empirically with a broad-spectrum antibiotic.WHAT THIS STUDY ADDSThis study will investigate if a cough swab or an induced sputum sample is a useful alternative to bronchoalveolar lavage (BAL) samples obtained during flexible bronchoscopy (FB-BAL) for the identification of the causative organism(s) in children with PBB.HOW THIS STUDY MIGHT AFFECT RESEARCH, PRACTICE OR POLICYIf either or both of the two non-invasive strategies are shown to be a useful alternative to FB-BAL, this will lead to more children with PBB having lower airway samples enabling targeted antibiotic prescribing and reducing the need for FB.

## Introduction

Protracted bacterial bronchitis (PBB) is the leading cause of chronic wet cough in children from developed countries and the most common reason for referrals to UK Paediatric Respiratory clinics.^1 2^ It is caused by bacterial infection of the conducting airways.^3^ It is most prevalent in children aged 1–5 years but can occur up to the age of 10. The cough is persistent and troublesome. It affects the child’s sleep, school performance and physical activities.^4^ This has a detrimental effect on the child’s quality of life (QoL) and that of family members.^5^ Moreover, untreated PBB is associated with subsequent permanent airway damage (bronchiectasis)^6 7^ causing long-term morbidity and increasing healthcare utilisation.^8^

The original diagnostic criteria (now called PBB-micro) were: (1) wet cough >4 weeks, (2) culture of a respiratory pathogen from a lower airway sample and (3) cough cessation after course of appropriate oral antibiotic.^2^ Commonly causative pathogens include: *Haemophilus influenzae*, *Streptococcus pneumoniae*, *Moraxella catarrhalis* and *Staphylococcus aureus*.^9^ As children with PBB rarely expectorate sputum, the only widely used method to sample the lower airway is bronchoalveolar lavage obtained during flexible bronchoscopy (FB-BAL). This is invasive, requires a general anaesthetic and causes significant disruption to families.^10^ Due to the large number of children presenting to Paediatric Respiratory clinics with PBB, it is not practical to undertake FB-BAL in all cases. An alternative diagnostic criteria was therefore developed (PBB-clinical) in which the need for ‘culture of a respiratory pathogen from a lower airway sample’ was replaced with ‘absence of symptoms or signs of other causes of wet cough’.^11^ FB-BAL is now only undertaken in children with PBB if their symptoms fail to improve with the initial treatment or frequently relapse.^12^

Due to the issues in obtaining lower airway samples, the majority of children diagnosed with PBB are started on a treatment without microbiology data to inform the choice of antibiotic.^12^ This means a broad-spectrum antibiotic such as co-amoxiclav has to be used.^13^ When microbiology data are available, it allows a narrower spectrum antibiotic to be used which decreases the risk of antibiotic resistance.^14^ If a non-invasive, child-friendly method of sampling the lower airway was shown to be effective in providing microbiology data for children with PBB, it would mean less FB-BAL would be required reducing the disruption to families. It would also enable lower airway samples to be obtained in more children enabling antibiotic prescribing to be targeted, reducing antibiotic resistance. Data from trials in children with cystic fibrosis (CF)^15^ suggest that there may be a role for cough swabs or induced sputum samples in PBB, this cannot be assumed without undertaking a study.

### Objectives

The primary objective is the discordance in pathogen yield between cough swab/induced sputum and FB-BAL.

The secondary objectives are as follows:

To calculate the sensitivity of each sampling technique (cough swab, induced sputum and FB-BAL) to correctly identify all pathogens isolated from the lower airway in children with PBB.To report the success rate of obtaining a usable induced sputum sample in children with PBB.To report the tolerability of the three sampling measures (cough swab, induced sputum and FB-BAL).

### Outcomes

The primary outcome is the discordance in pathogen yield between cough swab/induced sputum and FB-BAL.

The secondary outcomes are as follows:

The sensitivity of each sampling technique estimated using triplicated (cough swab/induced sputum/FB-BAL) culture results as gold standard.The success rate of obtaining a usable induced sputum sample in children with PBB as recorded by the physiotherapist in the study case report form (CRF).The tolerability of the three sampling strategies (cough swab, induced sputum and FB-BAL) as recorded on Likert scale questionnaires.

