### Statistical data analysis

#### Sample size calculation

The sample size was calculated using the McNemar’s test^16^ for paired proportions, informed by the comparison of pathogen yield from paired induced sputum and six-lobe FB-BAL samples in the CF-SPIT study.^15^ Assuming a proportion of discordant pairs of 0.37 we require a sample size of 110 to detect a ratio of discordant proportions (identification of an organism(s) on FB-BAL not isolated on induced sputum vs identification of organism(s) on induced sputum not identified on FB-BAL) of 3, with 90% power and 0.05 significance. If we assume the same induced sputum success rate as CF-SPIT (84%), we need a final sample size of 131. The sample size required to detect a difference between cough swab and FB-BAL is smaller due to a higher proportion of discordant pairs.

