#### Primary outcome analysis

The organisms isolated from each participants cough swab will be compared with those isolated from their FB-BAL samples to identify concordance/discordance. The pathogen yield is concordant if the same organism(s) are identified in both samples or no organisms are identified in either. If the same organisms are not identified in both samples the pathogen yield is discordant. Discordance will be classified as CS^+^/FB-BAL^−^ when an organism is isolated on cough swab but not on FB-BAL or CS^−^/FB-BAL^+^ when an organism is isolated on FB-BAL but not on cough swab. This will be repeated with the FB-BAL organisms limited to those from a single lobe (RML) and two lobes (RML and LLi) to allow comparison of pathogen yield if a more limited FB-BAL sampling methodology had been used. The same analysis will be undertaken to identify concordance/discordance between the induced sputum and the FB-BAL samples.

We will use conditional logistic regression analyses to estimate the OR of discordant proportions for the paired cough swabs and FB-BAL samples (identification of an organism(s) on FB-BAL not isolated on cough swab vs identification of organism(s) on cough swab not identified on FB-BAL). This will be analysed separately using FB-BAL results from one, two and six lobes. A similar analysis will be undertaken for the paired induced sputum and FB-BAL samples.

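### The named primary outcome is discordance, but the only primary estimate is the ratio of its two directions, which does not measure how much discordance there is

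*Protocol article*

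**What the plan says.** The Abstract, Objectives and Outcomes of the protocol article agree on the target. The Objectives section reads "The primary objective is the discordance in pathogen yield between cough swab/induced sputum and FB-BAL", and the Outcomes section repeats it as the primary outcome: "The primary outcome is the discordance in pathogen yield between cough swab/induced sputum and FB-BAL".

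Primary outcome analysis defines agreement by organism identity: "The pathogen yield is concordant if the same organism(s) are identified in both samples or no organisms are identified in either". Every other pair is discordant and is labelled by direction, for the cough swab and likewise for induced sputum.

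The estimate that follows is different in kind: "We will use conditional logistic regression analyses to estimate the OR of discordant proportions for the paired cough swabs and FB-BAL samples". The contrast is spelled out as "identification of an organism(s) on FB-BAL not isolated on cough swab vs identification of organism(s) on cough swab not identified on FB-BAL". It is planned for one, two and six lobes, and for sputum "A similar analysis will be undertaken for the paired induced sputum and FB-BAL samples".

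Sample size calculation uses the same ratio: "Assuming a proportion of discordant pairs of 0.37 we require a sample size of 110" in order "to detect a ratio of discordant proportions" of 3 by McNemar's test, with 90% power and 0.05 significance. Dividing by an 84% sputum success rate gives 131.

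Secondary outcomes analysis adds the sensitivity of each technique, with 95% score CIs. The reference is all pathogens found on any of the three samples, and a technique succeeds only if it finds every one.

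**The concern.** An outcome called discordance leads the reader to expect a result such as the share of children in whom the two samples disagree. The planned OR gives no such figure, because concordant pairs drop out of it. What remains is the balance between organisms found only on FB-BAL and organisms found only on the less invasive sample. The two directions offset each other in that ratio, whether the test-only organisms are contamination or true pathogens.

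The trial intends to say whether a swab or sputum sample could stand in for FB-BAL so that antibiotics can be targeted. That depends on whether the sample finds the organism that FB-BAL finds. Two samples can have equal yield while finding different organisms in different children. Conversely, a sample that nearly always agrees with FB-BAL can have a large OR if its few disagreements fall in one direction.

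**Working it through.** **1. What the trial is sized on.** Inputs from Sample size calculation: discordant proportion pd = 0.37, ratio 3, power 90%, alpha 0.05 (sidedness is not stated; two-sided assumed).

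- Ratio 3 splits 0.37 into 0.2775 and 0.0925, so d = 0.185.
- Unconditional McNemar formula: n = [1.96 × √pd + 1.2816 × √(pd − d²)]² / d² = [1.96 × √0.37 + 1.2816 × √0.3358]² / 0.0342 = 109.4, so 110.
- 110 / 0.84 = 130.95, so 131.

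Both stated figures reproduce. The trial is powered for asymmetry between the two directions, not for the precision of a discordance proportion.

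**2. What the OR depends on.** Let b be the children with an FB-BAL-only organism and c those with a test-only organism, among n pairs. For simplicity, let each discordant child be discordant in one direction only. Without covariates the conditional OR is b/c, and total discordance is (b + c)/n. With n = 110:

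| b v c | Total discordant (95% score CI) | Child has a missed FB-BAL organism | OR (exact 95% CI) |
|---|---|---|---|
| 5 v 5 | 10/110 = 9% (5–16%) | 5% | 1.0 (0.23–4.35) |
| 20 v 20 | 40/110 = 36% (28–46%) | 18% | 1.0 (0.51–1.96) |
| 45 v 45 | 90/110 = 82% (74–88%) | 41% | 1.0 (0.65–1.55) |
| 9 v 1 | 10/110 = 9% (5–16%) | 8% | 9.0 (1.25–394), p = 0.02 |

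The first three rows share an OR and differ ninefold in discordance. The first and last rows share a discordance and differ ninefold in OR. The OR interval is also narrower for 45 v 45 than for 5 v 5, so the null result looks firmest where agreement is worst.

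**3. How test-only organisms move the ratio.** Take b = 30 and c = 10: OR 3.0, missed 30/110 = 27%, total 40/110 = 36%. Now let 20 previously concordant children also grow a test-only organism, so c = 30. The OR falls to 1.0 and total discordance rises to 60/110 = 55%. The missed proportion stays at 27%.

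**4. Is this foreseeable?** The article's Discussion gives pathogen counts from the CF-SPIT study: 39 in total, of which induced sputum found 27, two-lobe FB-BAL 28 and six-lobe FB-BAL 33. Assume that the 39 are the union of sputum and six-lobe FB-BAL, and that the two-lobe isolates are a subset of the six-lobe isolates.

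- Six lobes: FB-BAL-only 39 − 27 = 12; sputum-only 39 − 33 = 6; ratio 2.0; sputum missed 12/33 = 36%.
- Two lobes: b − c = 28 − 27 = 1. The 6 sputum-only pathogens are also absent from two lobes, so c ≥ 6 and b ≥ 7. The ratio is at most 7/6 = 1.17, yet sputum missed at least 7/28 = 25% of the two-lobe pathogens.

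These are pathogen counts, whereas the plan analyses children, so they are indicative only. They do show that a near-null ratio can sit beside substantial misses in one of the comparisons the plan intends to make.

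**5. What the same data would give directly.** At the planning value, 41/110 = 37% discordant has a 95% score CI of 29–47%.

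**The case against.** The strongest replies are these.

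- *The OR answers a stated aim.* The Abstract asks whether yields are comparable, and the McNemar sizing and the OR fit that aim. This stands: the OR is a valid test of equal yield. But the Outcomes section names discordance, and Primary outcome analysis defines it by organism identity. Equal yield is a weaker property than agreement.
- *Discordance is analysed, because every pair is classified.* The counts will exist and could be tabulated, and a condensed article may leave detail to a fuller document. That is why the repair is cheap. The point is not a missing detail, however: the article does fix a primary estimate, and that estimate measures something else.
- *The sensitivity analysis shows missed organisms.* In part. A swab that misses an FB-BAL organism fails for that child, so 45 v 45 would show as poor sensitivity. But the analysis is secondary, and its reference pools organisms from all three samples. It does not give the proportion of children with an FB-BAL organism missed by the test.
- *Test-only organisms may be real.* For sputum, the Discussion takes this view, attributing such isolates to FB-BAL sampling the larger airways poorly. Calling them spurious would go beyond the document. The offsetting in the ratio is the same on either reading.

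A reader might also infer that the plan treats an OR near 1, or a non-significant OR, as proof of equivalence. No section says so: the sample size is for detecting a difference, and no criterion for usefulness is tied to the OR. Nor does the article give any rate of upper-airway carriage, so it cannot show that contamination will bring the swab's OR to about 1.

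**Conclusion.** The concern holds as a mismatch between the named primary outcome and its estimate. The outcome is the amount of discordance; the estimate and the power calculation address only its direction. An OR of 1.0 is compatible with 9% and with 82% discordance, and an OR of 9.0 with 91% agreement. The OR alone therefore cannot support a conclusion that either sample is a useful alternative to FB-BAL.

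This rests on the conditional OR being fitted without covariates, as described, and on counting each discordant child in one direction in the illustrations. It needs no assumption about carriage or about whether test-only growth is genuine. It does not make the OR invalid, and the sample size arithmetic is correct under a two-sided 0.05 level. The change should be made, but it is a matter of definition and reporting rather than a flaw in the design or data collection.

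**What to change.** In Primary outcome analysis, state as primary estimates, separately for cough swab and induced sputum against six-lobe FB-BAL, each with a 95% score CI:

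- (a) the proportion of children with an FB-BAL organism that the test missed;
- (b) the proportion of children with a test-only organism;
- (c) the total proportion of children discordant.

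A child can be discordant in both directions, so count such a child in both (a) and (b) but once in (c). As a result, (a) and (b) need not sum to (c).

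Keep the conditional OR and the powered McNemar comparison as the measure of direction. Add a sentence that an OR near 1 is not to be read as agreement, and base any statement about usefulness on (a), with (b) beside it.

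Cost: a wording change and slightly more reporting. The samples, the 2×2 tables and the target of 131 are unchanged.

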### Trial design

CLASSIC PBB is a multicentre clinical trial in which children with PBB, who are referred for a clinically indicated FB-BAL, will also have a cough swab and an induced sputum sample obtained.

### Trial setting

This is a multicentre study taking place in four UK children’s hospitals: Alder Hey Children’s Hospital (Liverpool), Great North Children’s Hospital (Newcastle upon Tyne), Sheffield Children’s Hospital and Staffordshire Children’s Hospital at Royal Stoke (Stoke on Trent).

### Participants

A total of 131 children (aged 1–10 years) with a clinical diagnosis of PBB who have been referred for a clinically indicated FB-BAL will be recruited from the four centres in accordance with the criteria shown in table 1. Patients will be identified from the paediatric respiratory clinics by the delegated local study team and paediatric respiratory consultants. In the clinic, a member of the study team will discuss the study with the parent/guardian and provide the relevant participant information sheet(s) (PIS). After sufficient time for consideration, patients/parents/guardians who wish to participate will provide informed, written consent and assent when appropriate.

**Table 1 T1:** Inclusion and exclusion criteria

Inclusion criteria	Exclusion criteria
Aged 1–10 years	Diagnosis of bronchiectasis, cystic fibrosis or immunodeficiency
Have a clinical diagnosis of PBB	FB-BAL being performed for a therapeutic indication (ie, lobar collapse) rather than for lower airway
Referred for a clinically indicated FB-BAL	Non-English speaker where translation facilities are insufficient to guarantee informed consent
Parent/guardian willing and able to give fully informed consent	Is taking part in another interventional study
Willing and able to comply with the study procedures	

BAL, bronchoalveolar lavage; FB, flexible bronchoscopy; PBB, protracted bacterial bronchitis.

### Trial assessments

The cough swab and induced sputum will be obtained on the same day and prior to the child’s FB-BAL by a delegated paediatric physiotherapist trained in the procedures. These procedures are aerosol generating so the local National Health Service (NHS) Trust guidelines regarding COVID-19 screening of children prior to admission and the use of personal protective equipment during the procedure will be followed.

#### Cough swab

The child will be instructed to tilt their head back and open their mouth wide. A sterile cotton swab will be placed at the back of the throat under the uvula and the child will be asked to cough. If the patient is too young to cough on command, the swab will be gently placed against the posterior pharynx to stimulate a cough. The sample will be labelled according to local guidelines and sent to the local microbiology.

#### Induced sputum

A 8 mL of 7% saline will be administered through a disposable oxygen-driven jet nebuliser set at a flow rate of 5 L/min for 15 min. Chest physiotherapy appropriate to the child’s age and ability to cooperate will be given during and after the nebulised therapy. Oropharyngeal suction will be used to obtain a sputum sample if the child is unable to spontaneously expectorate. The sample will be labelled according to local guidelines and sent to the local microbiology laboratory for culture. Oxygen saturations (SpO_2_) will be monitored before, during and after procedure. If the child develops wheeze or SpO_2_ drops<94%, inhaled or nebulised salbutamol will be delivered. The procedure will be discontinued if symptoms persist or SpO_2_ remains <94%.

#### FB-BAL

The FB-BAL is clinically indicated and will be performed as per standard of care and is therefore not a research procedure. It will be performed under general anaesthetic using the following methodology across all four sites. Once the bronchoscope is inserted, suction of secretions will be avoided before BAL to limit contamination with upper airway organisms. A single 10 mL aliquot lavage will be instilled and retrieved using a syringe attached to the bronchoscope channel in each of the six lobes (including lingula). The lavages will be undertaken in a specific order: right upper lobe, right middle lobe (RML), right lower lobe (RLL), left upper lobe, left lingular (LLi) and left lower lobe). The sample will be labelled according to local guidelines and sent to the local microbiology laboratory for culture.

#### Procedure tolerability

A four-question, Likert scale tolerability questionnaire will be completed after each of the three procedures. This will be done by the parent/guardian with input from the child when appropriate.

### Treatment of isolated organisms

The treatment of organisms identified from lower airway samples is not part of the study protocol. All results will be available for the local clinical team who will follow local guidance about the treatment.

### Microbiology samples

All microbiology samples (FB-BAL, cough swabs and induced sputum samples) will be handled and stored in-line with the UK Standards for Microbiology Investigations (UK SMI).

### Public and Patient involvement

CLASSIC PBB was developed to address the concerns of families related to the burden associated with FB-BAL. We undertook detailed interviews with the parents of 25 children with PBB who have undergone FB-BAL. They identified significant burden related to anxiety about the procedure, the need to take time off school/work and financial implications.^10^ These results highlighted the need to look for a non-invasive alternative to FB-BAL for children with PBB and have helped us decide on the topics for the parental assessment of tolerability. Three parent contributors helped develop the study methodology which was also presented to the Alder Hey Young Persons Advisory Group.

One of the parent contributors (EH) is PPIE lead for the study, a coapplicant on the funding application and coauthor on this paper. She has helped develop the PIS and consent/assent forms as well as being a member of the trial steering committee (TSC) where she will continue to be an advocate of parents and children. Once the study is complete, she will help in writing the plain English summary of the results.

